# UV light-mediated corneal crosslinking as (lymph)angioregressive pretreatment to promote graft survival after subsequent high-risk corneal transplantation (CrossCornealVision): protocol for a multicenter, randomized controlled trial

**DOI:** 10.1186/s13063-024-08011-1

**Published:** 2024-03-06

**Keywords:** Cornea, (Lymph)angioregressive preconditioning, Multicenter randomized clinical trial (RCT), Corneal transplantation, Crosslinking (CXL), Graft rejection, Neovascularization, High-risk corneal transplantation, Randomized controlled trial

## Abstract

**Background:**

Good vision highly depends on the transparency of the cornea, which is the “windscreen” of the eye. In fact, corneal blindness due to transparency loss is the second most common cause of blindness worldwide, and corneal transplantation is the main cure. Importantly, the cornea is normally avascular but can secondarily be invaded by pathological (blood and lymphatic) vessels due to severe inflammation, and the survival prognosis of a corneal graft mainly depends on the preoperative vascular condition of the recipient’s cornea. Whereas transplants placed into avascular recipient beds enjoy long-term survival rates of > 90%, survival rates significantly decrease in pathologically pre-vascularized, so-called high-risk recipients, which account for around 10% of all performed transplants in Germany and > 75% in lower and middle-income countries worldwide.

**Methods:**

This parallel-grouped, open-randomized, multicenter, prospective controlled exploratory investigator-initiated trial (IIT) intends to improve graft survival by preconditioning pathologically vascularized recipient corneas by (lymph)angioregressive treatment before high-risk corneal transplantation. For this purpose, corneal crosslinking (CXL) will be used, which has been shown to potently regress corneal blood and lymphatic vessels. Prior to transplantation, patients will be randomized into 2 groups: (1) CXL (intervention) or (2) no pretreatment (control). CXL will be repeated once if insufficient reduction of corneal neovascularization should be observed. All patients (both groups) will then undergo corneal transplantation. In the intervention group, remaining blood vessels will be additionally regressed using fine needle diathermy (on the day of transplantation). Afterwards, the incidence of graft rejection episodes will be evaluated for 24 months (primary endpoint). Overall graft survival, as well as regression of corneal vessels and/or recurrence, among other factors, will be analyzed (secondary endpoints).

**Discussion:**

Based on preclinical and early pilot clinical evidence, we want to test the novel concept of temporary (lymph)angioregressive pretreatment of high-risk eyes by CXL to promote subsequent corneal graft survival. So far, there is no evidence-based approach to reliably improve graft survival in the high-risk corneal transplantation setting available in clinical routine. If successful, this approach will be the first to promote graft survival in high-risk transplants. It will significantly improve vision and quality of life in patients suffering from corneal blindness.

**Trial registration:**

ClinicalTrials.gov NCT05870566. Registered on 22 May 2023.

## Introduction

### Background and rationale {6a}

The main treatment of corneal blindness is corneal transplantation, which is the most commonly performed type of transplantation, with more than 50,000 surgeries per year in Europe and about 9000 in Germany. Out of these, about 10% in Germany and more than 75% in lower and middle-income countries are so-called high-risk full thickness penetrating keratoplasties (pKPLs) with pathological corneal neovascularization (CoNV) including blood and lymphatic vessels in the recipient bed [1–5]. The ingrowth of CoNV into the normally avascular cornea abrogates the immune-privileged state of the cornea and significantly impairs graft survival [6–8].

Thus, transplant rejection rates depend on the degree of recipient CoNV and reach more than 50% in the first two years in high-risk eyes [6–9]. Rejection is the main cause of graft failure, leading to the recurrence of corneal opacification, loss of quality of life, inability to work or live independently, additional costs, and blindness. So far, no established approach reliably improves graft survival in high-risk patients, including Human leukocyte antigen (HLA)-typing or systemic immunosuppression. Therefore, an effective therapy to reduce the risk of corneal graft rejection and thereby improve graft survival would alleviate the disease burden and improve the quality of life of numerous patients.

Previously, we and others have shown that lymphatic vessels are even more important than blood vessels in mediating immune responses after high-risk corneal transplantation [10, 11]. In addition, using the murine model of high-risk corneal transplantation, we have recently demonstrated that preoperative regression of pathologic corneal blood and lymphatic vessels before transplantation (“(Lymph)angioregressive Preconditioning”) significantly improves graft survival [11–13].

We also demonstrated that corneal crosslinking (CXL) with Riboflavin as a photosensitizer, a technique routinely applied in the clinic to stabilize corneas, e.g., in keratoconus, leads to the regression of CoNV in the experimental setting and patient eyes [13–15]. Importantly, graft survival was significantly improved when subsequent corneal transplantation was performed in mice with previous CXL and in early clinical case reports [13, 14]. All previous studies, however, were experimentally or retrospective without controls and with small sample sizes. Our ITT aims to test the effectiveness of pretransplant (lymph)angioregression by CXL in improving graft survival in high-risk corneal transplant patients. This is the first prospective clinical trial in ophthalmology and transplant medicine in general concerning [lymph]angioregressive preconditioning of a transplant recipient site. Positive results could also benefit other areas of transplantation immunology [16, 17].

### Objectives {7}

The trial's primary objective is to prove and estimate the reduction of graft rejection rates and subsequent graft failure rates after corneal transplantation in vascularized high-risk eyes by preoperative (lymph)angioregressive pretreatment using CXL. Secondary objectives are functional graft survival rate, rejection-related graft failure rate, regression of pathological corneal vessels after CXL (after 1^st^ and eventually 2^nd^), number of CXL needed for successful regression > 50% of CoNV, recurrence of CoNV after CXL and after transplantation and visual acuity. Additional secondary endpoints are vision-related quality of life and safety.

### Trial design {8}

This trial is a parallel-grouped, open-randomized, multicenter, controlled exploratory ITT. Groups (intervention group [once or twice CXL] and control group [no CXL]) will be randomly allocated in a 5:4 ratio. One hundred and ten participants will be included in the trial (intervention group 61 patients, control group 49 patients).

### Participants

#### Study setting {9}

This multicenter clinical ITT will be conducted at seven sites in Germany (Berlin, Cologne, Duesseldorf, Freiburg, Homburg/Saar, Munich, and Rostock). If necessary, further qualified trial sites may be recruited for the trial. The listing of trial sites, principal investigators and investigators, and further trial staff will be kept and continuously updated on our homepage (http://augenklinik.uk-koeln.de/forschung/klinische-studien/). A final version of this list will be attached to the trial's final report.

#### Eligibility criteria {10}

Eligibility for patients: Male and female patients aged ≥ 18 years with pre-vascularized corneas ≥ 2 corneal quadrants with the need for corneal transplantation due to central corneal opacification and low visual acuity due to this condition can be included in the study.

Patients who qualify for the study and want to participate must sign a written informed consent (IC) before inclusion. Exclusion criteria include certain eye conditions (dysregulated glaucoma, active uveitis, or corneal ulcer), allergies, contraindications to medication or surgery, significant medical conditions, and inability to comply with the study protocol.

Eligibility for study centers and surgeons: All study centers must have at least one expert corneal surgeon. To ensure follow-ups and if repetition of CXL is needed, another ophthalmologist will be involved.

#### Who will take informed consent? {26a}

After completion of screening at visit one, patients will be informed verbally and in writing incomprehensible language about the nature, scope, and possible consequences of the surgery, the possible pretreatment with CXL, and the randomization by the local principal investigator/investigator. Patients will sign the IC to the trial, where all potential interventions and the randomization will be discussed before inclusion in the trial, as well as an IC form specific to keratoplasty at least 24 h before the pKPL operating day. All questions will be addressed.

The participant information materials and informed consent forms are available from the corresponding author on request. The signed consent form is archived as original in the investigator site file at the trial site. Trial patients receive copies of the written information sheet and the signed IC form.

#### Additional consent provisions for collection and use of participant data and biological specimens {26b}

So far, additional data or biological specimen sampling and analysis are not planned; however, this might change in the future. In case of any changes in the study design, the EC and renewed IC approval is required.

## Interventions and outcomes

### Explanation for the choice of comparators {6b}

Parallel groups will be randomly allocated to “CXL” versus “no CXL” before corneal transplantation in a 5:4 ratio; “no CXL” before corneal transplantation is the current standard treatment. There is no evidence-based, standardized, valid clinical method to improve corneal transplant outcome in high-risk patients. We chose CXL to precondition the recipients’ cornea as it has shown high efficacity in regressing CoNV and barely any side effects [14]. A sham CXL procedure will not be performed in this study.

### Intervention description {11a}

pKPL replaces all layers of the diseased central cornea with an allogeneic healthy graft from a deceased donor. pKPL will be performed as a standard full-thickness penetrating procedure, and the graft (individualized size between 6.5 and 8.25 mm in diameter) will be secured with at least 16 interrupted (or double running star-shaped) 10-0 nylon sutures.

CXL is a corneal treatment involving riboflavin and irradiating the cornea with UV-A light. An accelerated protocol is used, which involves higher illumination intensity (9 mW/cm^2^) and shorter UV-A irradiation time (10 min) [18]. A shield protects the limbus during the procedure to prevent damage to the limbal stem cells as we plan to irradiate the complete cornea. CXL will be performed in the intervention group to stabilize the recipient cornea and to reduce CoNV 8 to 10 weeks before pKPL. The control group will undergo pKPL without prior CXL. CXL can be repeated once at least 14 days before transplantation if CoNV is not completely regressed.

In case of residual CoNV on the day of transplantation, fine needle diathermy will be used in the intervention group. It involves coagulating blood vessels using a monopolar cautery unit and a bent needle. In the control group, no fine needle diathermy will be performed.

Postoperatively, all patients will be treated with topical corticosteroids and antibiotics, and a systemic carboanhydrase inhibitor will be given to reduce intraocular pressure on the transplant.

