### Participant timeline {13}

The planned participant timeline over the whole trial duration is shown in Table 1.

**Table 1 Tab1:** Timeline over the trial duration

First patient first visit (FPFV):	Quarter (Q) IV 2023
Last patient first visit (LPFV):	Q III 2025
Last patient last visit (LPLV):	Q III 2027
End of trial:	Q IV 2027
Final study report:	Q III 2028

The planned participant timeline of visits with procedures per visit and overview of the trial as a flowchart is shown in Table 2 and Fig. 1.

**Table 2 Tab2:** Participant timeline of visits with procedures

Visits	Screening	Baseline	Control after CXL^a^	Repeat study intervention^b^	Control after the second CXL	Transplantation^c^	FU				
Trial points	Week −14 to −10	Week −10 to −8	Week −8 to −6	Week −6 to −4	Week −4 to −2	D 0	Week 12±2 wk	Week 24±2 wk	Week 48±2 wk	Week 72±2 wk	Week 96±2 wk
Eligibility and history	X										
Informed consent	X										
In-/exclusion criteria	X										
Demographics	X										
Medical history	X										
Slit lamp exam	X	X	X		X		X	X	X	X	X
Standardized digital photo		X	X		X		X	X	X	X	X
Laser-FlareCell-Meter^d^		X					X	X	X	X	X
Corneal tomography	X	X	X		X		X	X	X	X	X
SL-OCT	X	X	X		X		X	X	X	X	X
Visual acuity	X	X	X		X		X	X	X	X	X
Concomitant medication	X	X	X		X		X	X	X	X	X
Randomization^e^	X										
Vision-related quality of life		X					X	X	X	X	X
CXL (intervention group only)		X		X							
Transplantation						X					
AE review and evaluation			X	X	X		X	X	X	X	X
Corneal endothelial count							X	X	X	X	X
Macula OCT^f^	X						X	X	X	X	X

*AE *Adverse event, *CXL *Corneal crosslinking, *FU *Follow-up, *EOT *End of trial, *SL-OCT *Slit lamp optical coherence tomography

^a^Two weeks after the first CXL, ^b^when regression of corneal neovascularization is < 50%, repeat CXL 4 weeks after first CXL, ^c^depending on availability of the graft and randomization, transplantation will take place between 8 and 10 weeks after baseline visit, ^d^optional (if available), ^e^after obtaining IC and completion of screening, ^f^if deemed necessary by the investigator

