#### Plans to promote participant retention and complete follow-up {18b}

The distinguishing intervention between the two study arms (CXL) will be performed after trial entry. All trial participants will be monitored closely by the study team. PKPL will be the same for both groups. Follow-up is usually excellent after transplant surgery with low loss-to-follow-up rates. These patients have a long medical/ ophthalmological history and generally only participate in clinical trials if they are highly motivated. Our patients attend regular follow-up visits, especially outpatient clinics anyway. We do not foresee any difficulties in completing the evaluation. Attrition bias will be minimized by sending timely reminders of follow-up appointments to patients and arranging substitutes for any missed visits. Patients do not need to adhere to any other specific tasks.

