Sufficient regression of CoNV after 1st CXL and only after 2nd CXL	Regression of CoNV > 50% (intervention arm only)	Value (yes/no)	Proportion	After 1st CXL and after 2nd CXL
Recurrence of CoNV	Recurrence (after sufficient regression was reached; intervention arm only)	Value (yes/no)	Proportion	After CXL (until transplantation) and after transplantation (within 24 months)
Visual acuity (BCVA)	ETDRS charts (transformed to logMAR)	Value	Mean	Prior to CXL, prior to transplantation, and 3, 6, 12, 18, and 24 months after transplantation
Vision-related quality of life	Overall score of NEI-VFQ25	Value	Mean	Prior to CXL, prior to transplantation, and 3, 6, 12, 18, and 24 months after transplantation
Infections	Active infectious keratitis or corneal ulceration	Value (yes/no)	Proportion	Within 24 months
Delayed wound healing	Delayed wound healing: corneal epithelium not closed (delay) or closed (no delay)	Value (yes/no)	Proportion	Within 24 months after transplantation
Graft dehiscence	Graft dehiscence characterized by leakage of aqueous humor	Value (yes/no)	Proportion	Within 24 months after transplantation

Survival analysis techniques will analyze primary and key secondary endpoints, allowing all patients to contribute information for however long they were followed up. The calculation of the scales of the NEI-VFQ follows the respective manual; missing values will be handled as described therein [19, 20].

The safety analysis includes calculating and comparing specified complication rates (see secondary endpoints), adverse events, and device deficiencies. Furthermore, descriptive methods are used to assess the homogeneity of the treatment groups. Analyses will be done using SAS (SAS Institute Inc., Cary, NC, USA) or IBM SPSS Statistics (IBM, Armonk, NY, USA).

Subgroup analyses will be done based on age at transplantation, sex, pretransplantation degree of CoNV, number of previous grafts, and presence of systemic immunosuppression.

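### The trigger for a second CXL is worded in two ways, and the objective and arm labels leave out the diathermy that only the intervention arm receives

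*Protocol article*

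**What the plan says.** On the second CXL, the article has three wordings:

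- Intervention description {11a}: "CXL can be repeated once at least 14 days before transplantation if CoNV is not completely regressed".
- Participant timeline {13}, Table 2, footnote b: "when regression of corneal neovascularization is < 50%, repeat CXL 4 weeks after first CXL".
- Abstract, Methods: "CXL will be repeated once if insufficient reduction of corneal neovascularization should be observed", with no number.

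The success criterion is set elsewhere. Objectives {7} lists the "number of CXL needed for successful regression > 50% of CoNV", and Table 3 in {20a} likewise scores sufficient regression as more than 50%, in the intervention arm only.

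On diathermy, the abstract and {11a} agree: vessels that remain on the day of transplantation are coagulated in the intervention group, and "In the control group, no fine needle diathermy will be performed". The Discussion describes the tested treatment as CXL with diathermy where additionally needed.

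The statements of aim and design do not carry this over. Objectives {7} ties the expected reduction in rejection to a reduction achieved "by preoperative (lymph)angioregressive pretreatment using CXL". Trial design {8} labels the arms as CXL once or twice against no CXL, and {6b} as CXL against no CXL. Section {18b} states: "The distinguishing intervention between the two study arms (CXL) will be performed after trial entry". It adds that the transplantation itself does not differ between the groups.

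**The concern.** The two issues are separate, but both concern what the intervention arm receives.

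First, the second CXL is part of the randomized intervention. Under {18a}, designated ophthalmologists at the sites decide whether regression suffices, and {9} names seven sites. With two thresholds in the text, one site may retreat an eye that another site leaves alone, and both can point to the protocol. Section {20a} also plans a frequency table of the CXL procedures required. If that table counts procedures delivered, its meaning depends on which threshold a site used.

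Second, diathermy is a vessel-regressing treatment given in one arm. The Discussion credits earlier evidence of vessel regression, and of better graft survival after it, to CXL or to diathermy. By the article's own account, diathermy could therefore contribute to the primary outcome. A reader who takes the objective and arm labels at face value would credit any benefit to CXL. The Discussion says that a confirmatory trial will follow success, so the misattribution could be carried into it.

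**Working it through.** No figure in the plan is at issue, so the check sets the sections side by side.

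**Step 1: the threshold.** Apply each wording to an eye seen at the control visit after the first CXL.

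| Regression after first CXL | {11a} | Table 2, footnote b | Success under {7} and Table 3 |
|---|---|---|---|
| below 50% | repeat permitted | repeat called for | no |
| above 50%, below 100% | repeat permitted | no repeat | yes |
| 100% | no repeat | no repeat | yes |

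The wordings part in the middle row. An eye at exactly 50% belongs there too: {11a} permits a repeat, footnote b does not call for one, and the eye is not yet a success. The abstract's unquantified wording does not settle the matter.

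**Step 2: timing.** Table 2 places the first CXL at week −10 to −8 and the repeat 4 weeks later, at week −6 to −4. The latest scheduled repeat is thus 4 × 7 = 28 days before surgery, which satisfies the 14-day minimum in {11a}. Timing is not in conflict.

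**Step 3: effect on the secondary endpoints.** Table 2 schedules a control visit two weeks after the first CXL, before any repeat. An eye above 50% at that visit is a success after the first CXL in Table 3, whether or not it is retreated later. That yes/no endpoint is unaffected. Only the count of required procedures in {20a} is open to two readings.

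**Step 4: what the arms receive.**

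| | Intervention (n = 61) | Control (n = 49) |
|---|---|---|
| First CXL | yes | no |
| Second CXL | conditional, threshold unclear | no |
| Diathermy on the day of surgery | if vessels remain | no |
| Transplantation | yes | yes |

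More than one row differs between the arms. The contrast estimates the effect of the whole strategy against none of it. No planned comparison separates the CXL part from the diathermy part.

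**Step 5: how the two issues meet.** Success means more than 50% regression, so a successful eye can still have vessels at surgery. Under footnote b such an eye is not retreated and, if vessels remain, goes to diathermy. Under {11a} it may be retreated first. The unsettled threshold can therefore also shift how many patients receive diathermy.

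**Step 6: size.** The number of eyes on which the two wordings part is 61 × (share with regression from 50% to below 100%). The document gives no such share, so the count can only be bounded between 0 and 61.

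**The case against.** The strongest reply is that this is loose wording in a condensed article. The sentence in {11a} is permissive and footnote b is directive. The objectives and Table 3 both use more than 50% as success, and the abstract can be read in line with that, so {11a} looks like the lone outlier. Diathermy is not hidden: the abstract, {11a} and the Discussion all state it. Comparing strategies is a legitimate design, the trial is labelled exploratory, and Data management {19} already lists single or repeated CXL, percentage reduction and diathermy among the items collected.

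Most of this stands, and it limits the point. It does not remove it. A permissive rule and a directive rule with different thresholds still leave the 50% to below 100% range to local choice. Disclosure elsewhere does not correct an objective and arm labels that omit a component given in one arm.

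Several stronger readings are tempting, and the document does not support them:

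- A reader might infer that the two timing statements conflict. They are compatible (step 2).
- A reader might infer that the regression endpoint is distorted by retreating eyes already above 50%. Table 3 scores it after the first CXL, so it is not (step 3).
- A reader might infer that the diathermy rule is itself inconsistent. It is the same wherever it is stated.
- A reader might take {18b} as an explicit claim that CXL is the sole difference. The sentence sits in a section on retention and mainly says when CXL takes place. It matters only because, with the arm labels and the statement on equal surgery, it leaves diathermy out.

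**Conclusion.** The point holds as two wording faults. The document gives two thresholds for the second CXL, so part of the randomized intervention is not uniquely defined for eyes with regression from 50% to below 100%. The objective and arm definitions also describe a narrower treatment than the one given. A difference in rejection would support a claim about CXL once or twice with diathermy for residual vessels, and not about CXL by itself.

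It would go too far to call the randomized comparison invalid. It remains a valid comparison of two strategies, and only its label and the conclusion drawn from it are affected. It would also go too far to put a number on the eyes affected by the threshold, since no regression distribution is given. Diathermy is possible in up to 61 patients in one arm and 0 of 49 in the other, and how many will receive it is likewise not stated. The conclusion rests on the article's text alone. The full protocol, which is not shown, may already state one threshold.

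**What to change.** - Reconcile the abstract, {11a} and Table 2, footnote b, into one threshold for the second CXL, and use the same threshold in the eCRF. Which threshold applies is for the clinical team. In {20a}, say whether the table of required procedures counts CXL delivered or CXL needed to pass 50% regression.
- Restate {7}, {8}, {6b} and {18b}, and the conclusion the trial intends to draw, as CXL once or twice plus diathermy for residual vessels against neither.
- Report by arm the share of patients receiving diathermy and the share receiving a repeat CXL, from the items listed in {19}.

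The cost is protocol wording and one descriptive table. No new data, visits or patients are needed. The real price is a narrower claim: the trial can speak for the strategy and not for CXL alone.
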